## Abstract

**Introduction:**

Diaphragm dysfunction is associated with failure to wean from mechanical ventilation. Inspiratory muscle training (IMT) may help improve outcomes for difficult-to-wean patients, yet the optimal approach remains unknown. High load IMT causes a training effect on the extra-diaphragmatic inspiratory muscles, but does not improve weaning success, questioning the utility of frequently cited high intensity IMT loads. Additionally, patients may find IMT unpleasant and distressing due to dyspnoea experienced during IMT. The aim of this study is to define a diaphragm-focused IMT load which is acceptable to patients.

**Methods:**

This study is designed as a prospective, mixed methods study. Forty difficult to wean, tracheostomised patients on mechanical ventilation will perform IMT at 15, 30, 45 and 60% of their maximal inspiratory pressure (PImax) in a randomised order using a tapered flow resistive loading device (POWERBreathe KH2, POWERBreathe, UK). Electrical activity of the diaphragm will be measured using an oesophageal multipair catheter (NAVA, Getinge, Sweden); extra-diaphragmatic (parasternal, scalene and sternocleidomastoid) muscle activity will be measured using surface electromyography. Patient experience of each load will be explored by measuring perceived breathing difficulty and unpleasantness using 0–10 numeric rating scales, verbal or written communication techniques in line with the participants' communication ability, and/or bespoke communication boards co-designed with the study patient and public involvement (PPI) group. Quantitative and qualitative data will be integrated to inform a diaphragm-focused, patient-acceptable IMT load.

**Ethics and dissemination:**

Ethical approval was obtained from Wales Research Ethics Committee 4 (Reference 25/WA/0242) on 30 October 2025. Results from this study will be presented at scientific meetings and published in peer-reviewed journals.

**Trial registration number:**

NCT07256821.

WHAT IS ALREADY KNOWN ON THIS TOPICPrevious work evaluating inspiratory muscle training (IMT) in mechanically ventilated patients has shown variable effects on strength and clinical outcomes, with training regimes often lacking a clear physiological basis and studies disregarding the patient experience.WHAT THIS STUDY ADDSThis prospective, mixed methods study will examine the electrical activity of the diaphragm and selected extra-diaphragmatic muscles during four IMT intensities. Patient experience of IMT will be explored contemporaneously using a bespoke range of communication approaches.HOW THIS STUDY MIGHT AFFECT RESEARCH, PRACTICE OR POLICYQuantitative and qualitative data will be integrated to determine an IMT load that focuses on diaphragm activation and is psychologically acceptable to patients.The results of this study will be used to inform the design of a feasibility randomised controlled trial.

## Introduction

 Critically ill patients undergoing mechanical ventilation (MV) frequently develop diaphragm dysfunction. Diaphragm dysfunction is present in 63–80% of patients mechanically ventilated for over 48 hours^1 2^ and is associated with prolonged ventilation, increased mortality and readmission to intensive care (ICU).^13^,^7^ Patients who require prolonged ventilation (‘difficult to wean’ patients) have increased long-term cognitive and functional impairments, poorer post-discharge survival,^5 8^ occupy a disproportionate number of ICU bed days and have greater healthcare costs.^9 10^

Inspiratory muscle training (IMT) has been proposed as a treatment strategy to improve outcomes in difficult to wean patients by improving the strength and endurance of the diaphragm through the application of resistance during inspiration.^11^ IMT has been shown to improve overall volitional inspiratory muscle strength (PImax) in many studies; however, three systematic reviews have concluded there is insufficient evidence to confirm whether it has a positive effect on clinical outcomes such as weaning duration and ICU and hospital length of stay.^12^,^14^ Furthermore, a large randomised controlled trial (RCT) recently conducted by Van Hollebeke *et al* found no significant differences in PImax or weaning success following sham versus high load IMT in difficult to wean patients.^15^

One reason why studies may fail to consistently find an effect with IMT is due to the heterogeneity of training approaches employed^16 17^; training regimes vary widely across the literature employing endurance or strength-based training at loads set anywhere between 20 and 50% of the patient’s PImax, often increased to the maximum tolerable by the patient.^1518^,^23^ Most studies lack a clear physiological basis for the training regime chosen. Importantly, it is specific diaphragm weakness that is associated with weaning failure in mechanically ventilated patients, not overall inspiratory strength. IMT will not only target the diaphragm but also the extra diaphragmatic inspiratory muscles, to a greater extent as the load increases.^24^ High load IMT is frequently used in difficult to wean patients,^15 19 21 22^ causing a training effect on the scalene and sternocleidomastoid muscles,^25^ but does not improve weaning success,^15^ perhaps unsurprising as extra-diaphragmatic muscles are not useful for sustained ventilatory effort in mechanically ventilated patients.^16 26 27^ As IMT load increases, so does the metabolic demand on the patient, for possibly no physiological benefit.^28^

It has been proposed that a high load, interval approach to IMT is ideal for mechanically ventilated patients to briefly load the inspiratory muscles.^29^ However, high load IMT (breathing forcefully) may cause patients to experience dyspnoea, a sensation consistently associated with the fear of dying in mechanically ventilated patients.^30 31^ Patient and public involvement (PPI) in the planning of this project identified that high load IMT can be unpleasant and distressing. These factors may explain the variable completion rates of planned high load IMT sessions reported in the literature (between 17 and 88%), with patient refusal or fatigue commonly cited as the reasons for non-adherence.^15 19 22^ An IMT load that patients find acceptable may help reduce the negative short and long-term effects of dyspnoea, which could be caused by IMT, such as immediate distress^31 32^ or longer term post-traumatic stress disorder.^33^ In turn, an acceptable load may reduce refusal rates, enhancing the efficacy of the intervention.

There are calls for the optimisation of the IMT stimulus in difficult to wean patients using the principles of muscle physiology and exercise prescription^16 17 25^; hence, this study aims to define not only a physiologically informed IMT load which focuses on training the diaphragm but also, importantly, a load which is acceptable to patients.

The objectives of this study are as follows: (1) Measure diaphragm and extra diaphragmatic (parasternal intercostal, scalene and sternocleidomastoid) inspiratory muscle activity using electromyography (EMG) during four different IMT loads in tracheostomised, difficult to wean, patients. (2) Explore the experience of these varied IMT loads using difficulty and unpleasantness numeric rating scales (NRS) and qualitative methods in line with the participants’ communication ability. (3) Integrate quantitative and qualitative data to determine a diaphragm-focused and patient-acceptable IMT load.

## Methods and analysis

### Patient and public involvement (PPI)

A PPI group was formed in the planning stages of this study, consisting of one relative of an ICU survivor and six ICU survivors, all of whom experienced prolonged mechanical ventilation in ICU. Five members had performed IMT when mechanically ventilated. The PPI group met with the research team on 12, 1-hour long occasions; their participation was fully remunerated in line with the NIHR payment guidance for public contributors.^34^

PPI was integral to the design of the study. Group members offered their lived experience of IMT when mechanically ventilated, including the following recollections: ‘mild training almost pleasant, extreme training like dying’, ‘they (IMT) were hard tasks, my chest felt tight and I felt very tired’, ‘not understanding what and why’, ‘recollections of breathing training formed hallucinations, dreams and nightmares’. Following this feedback, the study was changed from a physiological study measuring muscle activity only into a mixed methods study, reflecting the importance of patient experience when seeking the optimal IMT load.

The group understood the value of the research and felt they or their next of kin would consent to the study. The group advised for a longer period for qualitative data collection as they felt participants would be fatigued and breathless after IMT. They offered first-hand accounts of their changing cognition in ICU and suggested one to three research occasions per participant to improve the quality of the qualitative data and account for variable engagement. The group gave key words describing their experience of IMT or ventilator weaning (if they had not performed IMT). Over a period of six, hour-long PPI meetings, they co-designed the picture and word boards and numerical rating scale (NRS) anchors (online supplemental figures 1–6) that will be used to help participants describe how they experienced each IMT load. The group will help co-produce dissemination material and provide guidance on dissemination methods to reach wider patient communities.

### Trial design and setting

Prospective, mixed methods study that will be conducted on five medical, surgical and transplant ICUs within Guy’s and St Thomas’ NHS Foundation Trust, UK.

### Eligibility criteria

Patients will be eligible if they are mechanically ventilated via a tracheostomy; aged ≥18 years; co-operative and able to participate in IMT. Participants must be able to give informed consent or, in cases where the patient lacks capacity, surrogate approval will need to be granted by a personal consultee (a relative or friend). Exclusion criteria are as follows: facial or skull fracture, or a bleeding disorder, which would prohibit oesophageal catheter placement; undrained pneumothorax/pneumomediastinum; delirium or deep sedation that impedes the patient’s ability to participate in study procedures; pregnancy; unlikely to survive or attending consultant assessment that the patient is not appropriate.

### Recruitment

An electronic patient record (Epic Systems Corporation, Wisconsin, USA) will be used to screen for patients eligible for the study. Researchers will access this record daily to ensure eligible patients can be identified and approached about the possibility of participating in the study.

### Study procedures

#### Measurement of inspiratory muscle activity

Electrical activity of the diaphragm (EMGdia) will be measured using an oesophageal multipair catheter (NAVA, Getinge, Sweden), inserted according to manufacturer guidelines. The catheter will be inserted into the participant’s nose and passed into the stomach using the distance from the nasal bridge to the earlobe to xiphoid process measurement. The catheter will be connected to a ventilator (Servo-I, Getinge, Sweden), loaded with software (Servotracker, Getinge, Sweden), to verify catheter placement and to perform amplification and digital processing of EMGdia signals using the system’s proprietary algorithms. The Servo-I will only be used for acquisition of EMGdia data, not for mechanical ventilation.

Parasternal intercostal, scalene and sternocleidomastoid muscle activity will be measured using surface electromyography (sEMG). Skin will be prepared by shaving the area (if necessary) and lightly abrading the skin with Nuprep skin preparation gel (Weaver and Company, Aurora, USA) before wiping with an alcohol-impregnated wipe to remove sebum and dead skin cells before application of silver-silver-chloride electrodes. Parasternal intercostal EMG will be obtained with electrodes positioned over the second intercostal space bilaterally.^35^ Scalene and sternocleidomastoid electrodes will be positioned over the inferior portion of each muscle as previously described.^36^ EMG signals will be amplified (gain 1000) and band-pass filtered (20–1000 Hz with additional 50 Hz adaptive mains filter, (BioAmp amplifier, ADInstruments, Sydney, Australia)) and digitised (sampling frequency 2 kHz, PowerLab 16/35, ADInstruments, Sydney, Australia) before being displayed on a laptop computer for analysis.

Root-mean-squared values of EMG signals will be calculated in LabChart 7 (ADInstruments, Sydney, Australia) and Servotracker (Getinge, Sweden) and mean peak RMS EMG value per breath at each IMT load will be expressed as a ratio to that obtained while breathing during unsupported spontaneous breathing.

#### Airway pressure and flow

Respiratory flow (with derived volumes) will be measured continuously throughout the study protocol using a standard pneumotachograph (4700 series, Hans Rudolph Inc, Shawnee, USA) attached to a pressure transducer (Spirometer, ADInstruments, Sydney, Australia). A side port will measure pressure at the airway opening (MK1S, GM Instruments, Irvine, UK). Both signals will be digitised (sampling frequency 100 Hz, PowerLab 16/35, ADInstruments, Sydney, Australia) and displayed on LabChart7 software (ADInstruments, Sydney, Australia).

#### Maximal inspiratory pressure

PImax will be measured on each study occasion with the participant positioned in a semi-recumbent position in bed using a unidirectional valve (Hans Rudolph Inc, Shawnee, US) attached to the participant’s tracheostomy tube. The valve allows exhalation but occludes inspiration. In a method described by Marini and colleagues,^37^ participants will be encouraged to inhale repeatedly as forcefully as possible for 20 s. The valve will be connected to a pressure transducer (MK1S, GM Instruments, Irvine, UK), and data displayed on LabChart7 software. Measurement will be repeated at least three times, until three measures within 10% of each other are obtained,^38^ with a 2-min rest in between manoeuvres. The greatest peak pressure will be used for analysis.

#### Other assessments

Date of ICU admission, date of onset of mechanical ventilation, date of tracheostomy insertion, admission diagnosis, past medical history, Acute Physiology and Chronic Health Evaluation score (APACHE II) for the first 24 hours of admission, and Sequential Organ Failure Assessment (SOFA) score on each study occasion will be obtained from the patient’s electronic health record. Ventilation parameters (mode, Positive End Expiratory Pressure (PEEP); pressure support; peak inspiratory pressure; respiratory rate (set and spontaneous); tidal volume; minute volume; FiO_2_) and cardiovascular parameters (blood pressure, heart rate, vasopressor use) will be obtained on each study occasion. Airway occlusion pressure at 100 milliseconds (P0.1), and expiratory occlusion pressure (Pocc) will be measured on each study occasion using built-in functions on the participant’s ventilator.

#### Breathing conditions measured

Respiratory muscle activity, airway pressure and airway flow will be measured during the following breathing conditions: (1) spontaneous breathing supported by mechanical ventilation with pressure support, with settings maintained unchanged from those determined by the attending intensivist; (2) unsupported spontaneous breathing through tracheostomy after disconnection from mechanical ventilation; (3) during four IMT loads.

During spontaneous breathing supported by mechanical ventilation, the participant will receive no additional instructions from the researcher; measurements will be taken for 5 min. During unsupported spontaneous breathing and IMT, the participant will be informed that their breathing will feel harder. The researcher will count each of the ten breaths at each IMT load to guide the participant. Participants will be coached to exhale fully prior to each IMT breath and be given strong verbal encouragement to inhale forcefully against the applied resistance to generate tidal volume up to a comfortable deep inspiration at their own pace; no set breathing frequency will be imposed.

IMT will be performed using a tapered-flow resistive loading device (POWERbreathe KH2, POWERbreathe, Southam, UK). Participants will perform IMT at 15, 30, 45 and 60% of their maximal inspiratory pressure (PImax) in a randomised order (Sealed Envelope, Oxford, UK). The IMT loads chosen are based on preliminary data from healthy participants (study approved by Brunel University of London: reference 45378-MHR-Jan/2024-49666-3; manuscript in preparation)**,** where we found an increase in diaphragm activity with increasing IMT load, which, from 30–40% of PImax was accompanied by a proportionally greater increase in extra-diaphragmatic muscle activity. We have therefore chosen loads spanning the inflection point seen in healthy participants, with the aim of identifying a load which maximises diaphragm activity but which minimises accessory muscle activity.

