#### Exploring the patient experiences and perspectives of IMT load

Participant experience of IMT will be explored after each load. As participants will have a range of communication abilities, the researchers will work with speech and language therapists and staff in the ICU to optimise participants’ ability to communicate and express their experience of IMT. Communication methods will include the following: inline speaking valve, above cuff vocalisation, electrolarynx, bespoke communication boards, facial expressions, written communication and mouthing.^39^,^41^ An indicative topic guide to guide enquiry was co-developed and tested with the project’s PPI group.

Perceived breathing difficulty and unpleasantness will be measured using 0–10 numeric rating scales, as previously described^31^ with anchor points informed by the study PPI group: “0=none”, “10=extreme” for breathing unpleasantness (online supplemental file 1), “0=easy”, “10=extremely difficult” for breathing difficulty (online supplemental figure 2).

In participants who can phonate or respond using mouthing or written communication, following completion of the difficulty numeric rating scale (online supplemental figure 2), the participant will be asked “can you explain in words what that number felt like?” Due to the complexity of needs in this population, the researcher will use a range of strategies to enhance the depth of enquiry, such as confirmatory paraphrasing and summarising back to participants to check understanding of their response.

In participants unable to engage in independent expression of feelings as detailed above and to supplement information gained by verbal, written or lip reading, bespoke communication boards will be used (online supplemental figures 3–6). Within this complex population, when factors such as difficulty in phonating, breathlessness, weakness or fatigue with written communication limit answers, the bespoke communication boards will help improve the depth of information obtained. Contextual information (eg, participant gestures and the environment) will be captured using field notes, audio and/or video recording (subject to optional participant consent for video).

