### Data analysis plan

#### Quantitative

Data will be assessed for normality using histograms and the Shapiro-Wilk test. Baseline characteristics will be presented as mean (SD) or median (IQR). Mean peak root-mean-squared values of EMGdia, parasternal intercostal, scalene and sternocleidomastoid EMG for each load will be normalised as a ratio to that obtained during unsupported spontaneous breathing. For each individual muscle, the EMG activity between different IMT loads will be compared using a one-way ANOVA or Kruskal-Wallis test. To evaluate patterns of muscle activity between sEMG of the parasternal intercostal, scalene and sternocleidomastoid muscles and EMGdia, plots will be visually evaluated on Prism (GraphPad Software Inc, California, US) to identify the IMT load inducing maximum diaphragmatic contribution before the upward inflection point of accessory muscle activity.

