### Sample size calculation

This is the first study of its kind to measure inspiratory muscle activity and explore patient experience during different IMT loads in mechanically ventilated patients. No formal sample size calculation has been performed; however, based on data from the healthy study data conducted by our group, and accounting for the anticipated heterogeneity in the ICU population, we hypothesise that studying 40 participants will allow adequate exploration across one to three study occasions.

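### No completion or refusal measure is named for each load, and the unpaired EMG test cannot adjust if the highest loads are done only by more tolerant patients

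*Protocol article*

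**What the plan says.** All references are to the protocol article.

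- **Design** (*Breathing conditions measured*): "Participants will perform IMT at 15, 30, 45 and 60% of their maximal inspiratory pressure (PImax) in a randomised order". Each load is a set of ten breaths: "The researcher will count each of the ten breaths at each IMT load to guide the participant".
- **Experience** (*Exploring the patient experiences and perspectives of IMT load*): "Participant experience of IMT will be explored after each load". The measures are two 0–10 numeric rating scales (NRS), difficulty and unpleasantness, plus qualitative enquiry. Neither this section nor Table 1 lists breaths completed or refusal of a load. The withdrawal reasons given just before Table 1 concern leaving the study, not declining one load.
- **EMG summary** (*Measurement of inspiratory muscle activity*): the mean of the per-breath peaks at each load, as a ratio to unsupported breathing.
- **Comparison of loads** (*Data analysis plan, Quantitative*): for each muscle, "the EMG activity between different IMT loads will be compared using a one-way ANOVA or Kruskal-Wallis test". Plots are then read by eye for the load just before accessory activity turns upward. No test is stated for the ratings.
- **Background** (*Introduction*): earlier studies had "variable completion rates of planned high load IMT sessions reported in the literature (between 17 and 88%), with patient refusal or fatigue" as the common explanation. The same paragraph expects that an acceptable load could lower refusal.
- **Sample size**: 40 participants; "No formal sample size calculation has been performed".

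**The concern.** By the article's own reasoning, declining a load is direct evidence that it is not acceptable. Yet acceptability is to be judged from ratings and enquiry that follow a load, and nothing named in the article counts how often each load was declined or cut short. If some participants decline 60% of PImax, the ratings and EMG there come from those willing to attempt it, while 15% is described by nearly everyone.

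The stated test adds to this. One-way ANOVA and Kruskal-Wallis treat the four loads as four independent groups. A participant with values at 15, 30 and 45% but not at 60% adds nothing to the estimate at 60%, and the between-load contrast then mixes the effect of load with a change in who is measured. The test also ignores the pairing when nothing is missing.

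The study is meant to choose a load that will inform a feasibility trial, and that choice turns on the upper loads, where selection is most likely.

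**Working it through.** The article has no power calculation to reproduce. The check therefore asks how far the mean rating at a load could shift if those who decline it would have rated it worse.

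**Inputs**
- From the article: 40 participants, four loads, ten breaths each, and 17–88% completion in earlier studies. That range is for whole training sessions. It stands in here for the share of participants who give a rating at one load.
- Assumed, because the article gives no figure: NRS SD 2.5, and a correlation r of 0.3 to 1.0 between the rating and the tendency to refuse.

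**Formula.** If a share c contributes and the tendency to refuse is normal, the mean among contributors is too low by

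r × SD × φ(z_c) / c,

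where z_c is the normal quantile of c and φ is the normal density.

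| Share contributing (of 40) | φ(z_c)/c | r = 0.3 | r = 0.7 | r = 1.0 |
|---|---|---|---|---|
| 88% (35.2) | 0.227 | 0.17 | 0.40 | 0.57 |
| 70% (28) | 0.497 | 0.37 | 0.87 | 1.24 |
| 50% (20) | 0.798 | 0.60 | 1.40 | 1.99 |
| 17% (6.8) | 1.489 | 1.12 | 2.60 | 3.72 |

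The last three columns are NRS points. Example: 0.3 × 2.5 × 0.227 = 0.17.

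**Simulation check.** Scores were rounded and clipped to 0–10, with SD 2.5 before clipping, correlation 0.5 between loads, r = 0.7 and refusal at 60% only. The true means were 6.41 at 60% and about 5.00 at 45%, a difference of about 1.4 points.

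| Share contributing at 60% | Mean at 60%, contributors | Mean at 45%, everyone | Difference, available values | Mean at 45%, same contributors | Difference, same people |
|---|---|---|---|---|---|
| 88% | 6.07 | 5.00 | 1.07 | 4.81 | 1.26 |
| 70% | 5.62 | 5.00 | 0.62 | 4.58 | 1.04 |
| 50% | 5.10 | 4.99 | 0.11 | 4.32 | 0.78 |
| 17% | 3.92 | 5.00 | −1.08 | 3.76 | 0.16 |

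Each difference is the 60% mean minus the 45% mean beside it, for example 5.10 − 4.32 = 0.78. The shift at 60% (6.41 − 6.07 = 0.34 at 88%; 6.41 − 5.10 = 1.31 at 50%) is slightly below the formula's 0.40 and 1.40, as expected with clipping.

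**Reading.** Comparing available values shrinks the gap between loads, nearly removes it when half contribute, and reverses it at the extreme. Comparing the same people recovers part of the gap but not all, because refusal here depends on the unseen rating at 60% itself. Pairing therefore helps but does not replace a count of who declined.

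**EMG.** No size is given. The article offers nothing on whether those who decline would have had higher or lower normalised activity.

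**The case against.** Much can be said for the article as it stands.

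- **No rule discards unfinished loads.** A reader might infer that refused and unfinished loads both drop out of the data. The text does not say so. A mean peak per breath can be formed from fewer than ten breaths, and enquiry after a load does not require that all ten were done. Only outright refusal necessarily leaves no EMG and no rating. This stands.
- **Refusal may be captured informally.** Field notes, recordings and up to three occasions give chances to observe it or to obtain the load another day. This stands in part: a note is not an outcome tabulated by load.
- **The 17–88% range is for whole sessions.** Participants here must be co-operative and able to do the training, and the task is ten breaths, so non-completion may be much lower. This stands, and the 17% row is an extreme, not a forecast.
- **The direction for EMG is not established.** A reader might infer that only stronger patients will reach 60% and that EMG there will be too low. Loads are scaled to each person's own PImax and EMG to their own unsupported breathing, and a fatigued patient could show lower activity. This stands.
- **The unpaired test is stated for EMG only.** The rating calculation illustrates selection among available values; it does not show an error in a stated test of ratings. This stands.
- **The article is condensed.** Rules for incomplete data may sit in the full protocol or analysis plan, and silence on them is no fault. But the independent-groups test is stated, and so is the set of measures, in a study whose background makes refusal the central problem.

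**Conclusion.** The point holds in a limited form. Two stated features fit badly with the aim: the named measures leave out completion and refusal at each load, and an independent-groups test is applied to EMG from loads that each participant performs. If high loads are refused, results at 45 and 60% of PImax may come from a more tolerant subset, and the stated test has no means of adjusting.

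The size rests on assumptions. With SD 2.5 and r from 0.3 to 1.0, the mean rating is too low by about 0.2 to 0.6 points at 88% contributing and 0.6 to 2.0 at 50%. That is minor if nearly everyone attempts every load, and enough to hide a difference between loads if about half do not. The documents do not support the stronger conclusions that the plan throws away partial loads, that the session completion range applies to ten breaths, or that EMG at high load will be biased in a known direction. The change is worth making before data collection because it is cheap and bears on half of the study's aim.

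**What to change.** 1. At each load and occasion, record breaths completed and, where fewer than ten, whether the load was refused or stopped and why.
2. Report completion by load, with reasons, as an acceptability outcome beside the NRS in the joint display.
3. Keep EMG and ratings from partial loads, and state how many participants contribute at each load.
4. Replace the one-way ANOVA or Kruskal-Wallis comparison with a within-participant mixed model (participant random effect, load as a factor, all occasions) using every load attempted. It adjusts for refusal only so far as the observed loads predict it, so items 1 to 3 are still needed.
5. Do not code every stop automatically as not acceptable. With a randomised order, some stops may reflect fatigue carried over from an earlier load or an unrelated interruption; the recorded reason lets these be told apart.

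**Cost:** one extra form field, since breaths are already counted, and slightly more analysis work. No added procedure for participants.

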Participants will perform all study procedures on up to three occasions over a 7-day period. Reasons for earlier withdrawal would include decannulation from tracheostomy, weaning from mechanical ventilation, withdrawal of consent, or death. Table 1 provides an overview of study interventions and assessments performed during the study period.

**Table 1 T1:** Overview of study procedures

Study procedures	Study period	
	Day 0 (enrolment)	Each study occasion
Baseline characteristics	●	
SOFA score		●
Ventilation and cardiovascular parameters		●
Maximal inspiratory pressure (PImax)		●
Inspiratory muscle activity		●
Airway pressure and flow		●
Inspiratory muscle training		●
Perceived difficulty and unpleasantness (NRS)		●
Qualitative data enquiry		●

NRS, numerical rating scale; SOFA, sequential organ failure assessment.

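### The accessory-muscle inflection is located only by eye on loads 15 points apart, so a bend within 30–45% PImax cannot be placed and the load read off carries no uncertainty

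*Protocol article*

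**What the plan says.** Under Breathing conditions measured, the protocol article fixes the loads: "Participants will perform IMT at 15, 30, 45 and 60% of their maximal inspiratory pressure (PImax) in a randomised order". The choice rests on healthy-participant data in which diaphragm activity rose with load, and this rise "from 30–40% of PImax was accompanied by a proportionally greater increase in extra-diaphragmatic muscle activity". The stated rationale is: "We have therefore chosen loads spanning the inflection point seen in healthy participants, with the aim of identifying a load which maximises diaphragm activity", while keeping accessory activity low.

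Under Data analysis plan, Quantitative, the formal comparison is made muscle by muscle: "the EMG activity between different IMT loads will be compared using a one-way ANOVA or Kruskal-Wallis test". The pattern across muscles is handled differently: "plots will be visually evaluated on Prism", and the purpose is "to identify the IMT load inducing maximum diaphragmatic contribution before the upward inflection point of accessory muscle activity". The section gives no fitted model, reading rule or interval for that step.

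Under Sample size calculation no formal calculation is made: "we hypothesise that studying 40 participants will allow adequate exploration across one to three study occasions". The third objective in the Introduction combines the EMG result with patient experience to arrive at a load, and the key-messages box says the results will inform a feasibility randomised trial.

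**The concern.** The visual reading is the quantitative half of the study's aim. With four plotted loads, an upward corner can appear only at an interior load, 30% or 45%. Apart from its lower edge, the range in which the protocol expects the bend lies between those two. A bend there is shared between two corners, and the reader must decide which corner to believe or how to apply the word meaning ahead of the bend. ANOVA or Kruskal-Wallis can show that activity differs between loads, but not where its slope changes.

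The load that enters the integration with patient experience would therefore have no measure of how easily another sample, or another reader, would have produced a different one. This is a method that the article states, so it is not a detail left to an unseen analysis plan.

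**Working it through.** **Inputs from the protocol article.** Loads 15, 30, 45, 60%; healthy-participant inflection 30–40%; 40 participants; one to three occasions. The figure of 40 has no alpha, power, effect or SD behind it, so there is no calculation to reproduce.

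**Assumed, because the article gives neither.** Slope change at the bend, d = 0.02–0.04 units of the normalised EMG ratio per point of PImax; residual SD per load, s = 0.3–1.5; one occasion unless stated.

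**Step 1, geometry (no noise).** Let mean accessory activity rise linearly, with an extra slope d beyond a bend at τ between 30 and 45. The second differences at the interior loads are:
- at 30%: d(45 − τ)
- at 45%: d(τ − 30)

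As shares of the total 15d:

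| True bend | at 30% | at 45% |
|---|---|---|
| 30 | 100% | 0% |
| 35 | 67% | 33% |
| 37.5 | 50% | 50% |
| 40 | 33% | 67% |

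**Step 2, reading by sharpest corner.** The difference between the two corners is y₁ − 3y₂ + 3y₃ − y₄. Its mean is d(75 − 2τ) and its variance is (1 + 9 + 9 + 1)s²/n = 20s²/n. So P(pick 30%) = Φ( d(75 − 2τ) / (s√(20/n)) ).

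Example: n = 40, d = 0.04, s = 0.3, τ = 35. The numerator is 0.04 × 5 = 0.20, the denominator is 0.3 × 0.707 = 0.212, z = 0.94, P = 0.83.

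| True bend | P(pick 30%) over the assumed range |
|---|---|
| 30 | 0.61–1.00 |
| 32.5 | 0.57–0.97 |
| 35 | 0.54–0.83 |
| 37.5 | 0.50 always |
| 40 | 0.17–0.46 |

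If the bend also varies between patients with SD 10 points (s = 0.3–1.0), simulation gives 0.55–0.78 at 30, 0.54–0.62 at 35 and 0.39–0.49 at 40. With three independent occasions, a common bend, d = 0.04 and s = 0.3, it gives 0.95 at 35 and 0.06 at 40.

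**Step 3, reading by the written rule.** Take the highest tested load not above the bend. Without noise, every bend above 30% and up to 40% gives 30%. With noise (s = 0.3–1.0, least-squares broken line on the four means, bend searched up to 45%, simulated), the shares of studies are:

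| True bend | 15% | 30% | 45% |
|---|---|---|---|
| 35–40 | 0.00–0.36 | 0.35–0.99 | 0.00–0.35 |
| 30 | 0.43–0.53 | 0.33–0.50 | 0.00–0.24 |

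The 15% column needs care. With only one load to the left, every bend from 15% to 30% fits the four means equally well. On re-running the simulation, all of these picks were such ties, counted as below 30%. If the same tie is taken as a bend at 30%, the pick is 30%. The data cannot settle this, so the result turns on a convention that the protocol does not state.

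**Step 4, limits of a broken-line estimate.** Intercept, two slopes and a bend are four parameters on four load means, so the fit is saturated and its shape cannot be checked. For a smooth y = x² with no corner, the 15–30 line has slope 45 and the 45–60 line has slope 105. Setting 900 + 45(x − 30) = 2025 + 105(x − 45) gives 60x = 2250, so x = 37.5. Other convex quadratics give the same answer. An estimate near 37.5% is therefore not evidence of a bend there.

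**The case against.** A reader might infer that the plan's choice between 30% and 45% is close to chance. The documents do not support that as a general statement. The written rule asks for the load ahead of the upward inflection, not the load with the larger corner. Under it, a bend above 30% and up to 40% points to 30%, and 45% is chosen in at most about 0.35 of studies under the noisiest assumptions simulated. The even split is exact only at 37.5% and only under the corner reading. The SD and slope change behind every probability are assumptions. The protocol also allows repeat measurement, "Participants will perform all study procedures on up to three occasions over a 7-day period", which can make the choice far from chance away from 37.5%. This stands.

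It is also fair to say that 30% is itself a tested load, that the loads do span the healthy-participant range as claimed, and that the study is exploratory. The text does not say outright that the answer must be one of the four loads. Nor does the EMG reading fix the final load: it is combined with patient experience, and the results are said only to inform a later trial's design. Finally, unsupported breathing equals 1 on the ratio scale, and nothing bars it from the plots, so a reference level may be visible.

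None of this supplies an estimate of where the bend lies, a reading rule or an error. Two fair readings of the same plot can also disagree: with a bend at 40%, the corner reading favours 45% and the written rule gives 30%.

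**Conclusion.** The concern holds in limited form. By geometry alone, plots at four loads 15 points apart cannot place a bend within 30–45% without a model, and most of the protocol's own expected range lies there. From the text alone, the load read off has no uncertainty attached, and the only formal test does not address location.

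The size of the instability is conditional. By sharpest corner, the choice between 30% and 45% runs from near-certain to 50:50. By the written rule, a noise-free bend above 30% and up to 40% gives 30%, and the fragile case is a bend near 30%, where 15% and 30% compete and the outcome depends on how a tie is read. These probabilities rest on a broken-line truth and on assumed d and s. The point merits a change because the remedy is cheap and uses data already to be collected. No view is taken on which load is clinically right.

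**What to change.** Keep all four loads and all procedures, and change only the Quantitative section of the data analysis plan.

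1. Supplement the visual reading with a pre-specified within-participant analysis: log EMG ratio, a participant effect, and repeat occasions nested in participant. Estimate the slope of each accessory muscle relative to the diaphragm over each load step, and the change in slope at 30% and at 45%, with 95% confidence intervals from resampling participants.
2. Turn the rule for choosing the load ahead of the inflection into an operational one, including what happens when the change appears at a tested load. Apply it in every resample and report the share selecting each tested load.
3. Word the conclusion as the set of loads compatible with the data.
4. A broken-line estimate on the continuous scale may be added as a model-dependent secondary result. State that it is saturated with four loads, returns 37.5% for a smooth quadratic rise, and cannot identify a bend below 30%.
5. Adding unsupported breathing as a zero-load reference is a sensitivity analysis only, because that condition is uncoached.

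Cost: revised analysis wording and a few hours of programming. The downside is that the answer may be a range rather than one load.
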